Blood samples will be collected at baseline prior to vaccination and at 2 weeks post each dose vaccination for immunogenicity assessment (Day 0, Day 14, and Day 28).

Eligible participants enrolled in the study will be randomized into 4 study groups with age stratum of 1 to 5 years old, 6 to 17 years old, and 18 to 40 years old. Participants will be observed at the study site for 30 minutes after vaccination for immediate safety assessment. Solicited adverse events will be recorded during 7 days after vaccination. Unsolicited adverse events will be recorded within 28 days after vaccination. Serious adverse events will be reported during the entire study period.

Except for designated study site personnel responsible for vaccine administration, site investigators, study nurse, and those assessing clinical outcomes, and data analysts will be blinded to vaccine allocation until data base lock for the statistical analysis.

**Estimated Number of Participants to Enroll:** A total of 2,530 participants aged 1 to 40 years will be enrolled in this study. 2,530 participants will be randomized into 4 groups, 330 adult participants in group A and B each and 935 adult and children participants in group C and D each. Group C and D will be divided into age stratum of 1 to 5 years old, 6 to 17 years old, and 18 to 40 years old. Participants in the group A, B and C will receive OCV-S while participants in group D will receive Shanchol™. Group A, B and C are three different lots of OCV-S and group D is Shanchol™.

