| Diary Card (DC) Distribution            |                                                        | DC1 | DC2            | DC3     | DC4              | DC5               | DC6                |                      |                   |
| Diary Card (DC) Collection              |                                                        |     | DC1            | DC2**** | DC3              | DC4****           | DC5                | DC6                  |                   |
| Solicited Adverse Events                |                                                        |     | X              |         | X                |                   |                    |                      |                   |
| Unsolicited Adverse Events              |                                                        | X   | X              | X       | X                | X                 | X                  |                      | X                 |
| Study Completion Form                   |                                                        |     |                |         |                  |                   |                    | X                    |                   |
| SAE/Pregnancy Reporting                 | To be reported at any time throughout the study period |     |                |         |                  |                   |                    |                      |                   |

† 7 days post 1st dose vaccination

†† 7 days post 2nd dose vaccination

††† 28 days post 1st dose vaccination

†††† 28 days post 2nd dose vaccination

††††† 6 months post 2nd dose vaccination

\* Home visits/Phone calls

\*\* Pregnancy Test is necessary for all married female participants of childbearing age. If un-married female participants of childbearing age agree to take pregnancy test, the test should be performed.

\*\*\* After D42, concomitant medication history related to SAEs only will be recorded

\*\*\*\* For safety follow ups through phone calls, DC1,2 and DC 3,4 will be collected on V3 and V4, respectively.

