**Visit 3. 2nd dose Vaccination / Blood drawing (Day 14 / Week 2 + 3 days)**

- 1) Obtain medical/medication history and perform physical examination including vital signs and record in the eCRF.
- 2) Verify and record all unsolicited AEs and concomitant medications in DC2 and record in the eCRF.
- 3) Perform urinary pregnancy test for all married female participants of childbearing age. If unmarried female participants of childbearing age agree to take pregnancy test, the test should be performed.
- 4) Confirm eligibility of participant for the second dose vaccination.
- 5) Collect a venous blood sample prior to immunization; See Table below.

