**Visit 4. Post 1st dose 4-week Safety follow up / Blood drawing (Day 28 / Week 4 ± 3 days)**

Each participant will be followed up for safety and blood drawing.

- 1) Verify and collect DC4 and confirm with participant/parent(s)/LAR enter any unsolicited events and concomitant medications CRF
- 2) Provide DC5 to document unsolicited adverse events (if any occurrence is there) from Day 28 to Day 41. Instruct participant/parent(s)/LAR how to fill in the diary card.
- 3) If Day 42 visit will be through phone call, provide DC6 to record adverse events (if any occurrence is there) during Day 42 to Day 181.
- 4) Schedule next HV/PC3 at Day 42 and next visit to the study site at Day 182 and remind participant(s)/parent/LAR to bring the DC5 and DC6, if distributed, at the next visit. If HV/PC may not be applicable depending on situation (e.g., COVID-19 situation), it may be replaced by a site visit.
- 5) Instruct participant/parent(s)/LAR to contact investigator/study staff if needed.
- 6) Collect a venous blood sample prior to immunization; See Table below.

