#### 7.2.15 PROTOCOL DEVIATIONS

The ICH E3 Q&A R1 defines a protocol deviation (PD) as “any change, divergence, or departure from the study design or procedures defined in the protocol.” In other words, protocol deviation is any noncompliance with the clinical trial protocol, ICH E6 (R2) GCP, E11 (R1) or MOP requirements by the participant, the investigator, or the study site staff. It is the responsibility of the site PI to use continuous vigilance to identify and report all protocol deviations to the site IRB/IEC and to the sponsor. The PI is responsible for knowing and adhering to the site requirements. The IVI Study Medical Monitor will report all protocol deviations to IVI IRB/IEC and only major PDs have to be reported to IVI IRB/IEC within 10 calendar days of their awareness.

The ICH guidelines also introduce a definition for “important” protocol deviations, defining them as “a subset of protocol deviations that may significantly impact the completeness, accuracy,

and/or reliability of the study data or that may significantly affect a participant's rights, safety, or well-being." Important, "major", "critical" and "significant" are synonyms when referring to important protocol deviations.

To align the sponsor terminology with that of the health authorities' (*i.e.*, Regulatory Agency inspectors), we are using the terminology major and minor instead of the classification of important and non-important protocol deviations.

Major deviations are defined as those jeopardize the safety or rights of the participant or the scientific integrity of the study which is applicable to cases listed below.

- Violation of inclusion and exclusion criteria
- Vaccination with wrong vaccine as defined in the protocol
- Vaccination outside window of the immunization schedule defined in protocol
- Missed visit or visit outside window for the immunogenicity assessment

Major protocol deviations thought to affect the scientific integrity of the study and/or the safety and rights of the participant will be reported and discussed with investigator, monitor, sponsor, and statistician for their exclusion from the per protocol analysis.

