## 13. STATISTICAL CONSIDERATIONS

### 13.1 STUDY ENDPOINTS

#### 13.1.1 PRIMARY IMMUNOGENICITY ENDPOINT

- Proportion of participants showing seroconversion of vibriocidal titers against *Vibrio cholerae* O1 Inaba and O1 Ogawa (seroconversion is defined as at least 4-fold increase of vibriocidal titers against *V. cholerae* O1 Inaba and O1 Ogawa compared to baseline) at 2 weeks after second dose of either OCV-S (*i.e.*, one lot of OCV-S) or Shanchol™ for all ages.

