#### 13.1.3 SECONDARY ENDPOINTS

- Geometric Mean Titer of vibriocidal antibodies against *Vibrio cholerae* O1 Inaba and Ogawa 2 weeks after second dose of either OCV-S (*i.e.*, one lot of OCV-S) or Shanchol™ for all ages
- Proportion of participants showing seroconversion against *Vibrio cholerae* O1 Inaba and Ogawa 2 weeks after second dose of either OCV-S (*i.e.*, one lot of OCV-S) or Shanchol™ in each age stratum
- Geometric Mean Titer of vibriocidal antibodies against *Vibrio cholerae* O1 Inaba and Ogawa 2 weeks after second dose of either OCV-S (*i.e.*, one lot of OCV-S) or Shanchol™ in each age stratum
- Geometric Mean Titer of vibriocidal antibodies against *Vibrio cholerae* O1 Inaba and Ogawa 2 weeks after second dose of 3 lots of OCV-S in adults

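### The sample behind the endpoints at two weeks after dose 2 is scheduled from dose 1, so in-window intervals run from 8 to 17 days and the deviation rule treats equal intervals unequally

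*Protocol*

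**What the plan says.** Section 13.1.1 of the protocol sets the primary seroconversion endpoint "at 2 weeks after second dose of either OCV-S (*i.e.*, one lot of OCV-S) or Shanchol™ for all ages". Section 13.1.3 uses the same time point for the GMT comparisons, the age-stratum comparisons and lot consistency, the last being measured "2 weeks after second dose of 3 lots of OCV-S in adults". The synopsis describes the draws as taken "at 2 weeks post each dose vaccination for immunogenicity assessment (Day 0, Day 14, and Day 28".

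The schedule is built differently. Section 7.1.3 gives Visit 3 as 2nd "dose Vaccination / Blood drawing (Day 14 / Week 2 + 3 days". It titles Visit 4 Post 1st "dose 4-week Safety follow up / Blood drawing (Day 28 / Week 4 ± 3 days", and the Table 2 footnote to Day 28 reads "28 days post 1 st dose vaccination". The Day 21, Day 42 and Day 182 contacts are footnoted to the second dose. Visit 4 is thus the only follow-up after dose 2 that is tied to dose 1. No blood-draw window relative to dose 2 is given anywhere.

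Section 7.2.15 lists among the major deviations: "Missed visit or visit outside window for the immunogenicity assessment". Major deviations thought to affect integrity or safety are discussed for exclusion from the per-protocol analysis. Section 13.5 makes the per-protocol set (PPS) the primary set for immunogenicity, with the full analysis set (FAS) as sensitivity analysis.

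**The concern.** The endpoint clock starts at dose 2 and the sampling clock at dose 1. The two agree only when dose 2 falls exactly on Day 14. The dose 2 window is one-sided (+3 days), so lateness within it can only shorten the interval to a Day 28 sample. Some lateness is foreseeable, because sections 7.2.5 and 7.2.7 require vaccination to be postponed for fever, acute illness and other conditions.

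Two things are at stake. First, the titres in the non-inferiority and lot tests may come from a wider and earlier span than the stated time point. Second, the rule that feeds the PPS judges a sample by its distance from dose 1. It can therefore keep a sample far from two weeks after dose 2 and flag one much closer to it.

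**Working it through.** **Inputs.** Dose 2 day *d*: 14 to 17 (section 7.1.3, Visit 3). Visit 4 day *v*: 28 ± 3, so 25 to 31 (section 7.1.3, Visit 4; Table 2). Interval after dose 2 = *v* − *d*.

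**The plan's own figure.** On nominal days, 28 − 14 = 14 days, which reproduces the stated two weeks.

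**With both windows applied.** Minimum 25 − 17 = 8 days; maximum 31 − 14 = 17 days. The last column applies the protocol's own ±3-day tolerance to dose 2 instead of dose 1. That step is an assumption, because the protocol gives no such tolerance.

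| Dose 2 on | In-window interval (25 − d to 31 − d) | In window but below 11 days | Within 14 ± 3 days of dose 2 but outside Day 25–31 |
|---|---|---|---|
| Day 14 | 11–17 days | none | none |
| Day 15 | 10–16 days | Day 25 (10 days) | Day 32 (17 days) |
| Day 16 | 9–15 days | Days 25–26 (9–10 days) | Days 32–33 (16–17 days) |
| Day 17 | 8–14 days | Days 25–27 (8–10 days) | Days 32–34 (15–17 days) |

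**When intervals fall below 11 days.** Any Visit 4 on or after Day 28 is at least 28 − 17 = 11 days after an in-window dose 2. A shorter interval therefore needs a dose 2 on Day 15 to 17 together with a Visit 4 on Day 25 to 27. That is 1 + 2 + 3 = 6 of the 4 × 7 = 28 permitted date pairs. This counts calendar combinations; it does not estimate a share of participants.

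**Unequal treatment.** For a Day 17 dose, blood on Day 25 (8 days, 6 short of target) is in window, while blood on Day 32 (15 days, 1 over) is a major deviation. After a Day 14 dose, 15 to 17 days is Day 29 to 31 and in window.

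**Exact two-week samples.** *d* + 14 gives Day 28, 29, 30 or 31, all in window. Such a sample falls outside only if dose 2 was on Day 18 or later, and that dose is already a major deviation in its own right.

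**After re-anchoring to 14 ± 3 days from dose 2.** The Visit 4 windows become Days 25–31, 26–32, 27–33 and 28–34 for the four dose days, and every in-window interval is 11 to 17 days.

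**The case against.** The best defence is that the schedule works unless two departures combine in opposite directions. Participants dosed on Day 14 fall at 11 to 17 days, and no sample at exactly 14 days after an in-window dose is ever rejected. The Post 1st label could describe only the safety part of the visit. Section 7.2.15 names no anchor, PPS exclusion is discussed and not automatic, and FAS results are reported as well. Detailed sampling windows could sit in an analysis plan that is not at hand.

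Most of this stands as a limit on the size of the problem. It does not remove the contradiction: the Table 2 footnote anchors the whole visit to dose 1, the only printed window is Day 28 ± 3, and sites schedule from that table. An analysis plan could change which samples are analysed, but not when they were drawn.

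A reader might infer three stronger things, none of which the protocol supports:

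- *That about a fifth of participants are sampled too early.* The 6 in 28 would be a share of participants only if both visits spread evenly and independently over their windows, which would make 75% of second doses late. If instead 10% or 25% of second doses were late, with dates still spread evenly, 6/21 of those would give about 3% or 7%. All of these inputs are assumptions.
- *That the comparison is pulled toward no difference.* The windows are identical in all groups. Extra timing variation can also widen the GMT confidence intervals, which makes non-inferiority and equivalence harder to show. No direction is established.
- *That the result is materially changed.* Appended Table S3 shows, for Ogawa in adult Group A, seroconversion of 77.24% two weeks after dose 1 and 69.59% two weeks after dose 2, a gap of 7.65 points. If 3% to 7% of an arm moved by that whole gap, its rate would shift by about 0.2 to 0.5 points against a 10-point margin, and the difference between arms would be expected to shift less. This is only a rough scale, because the table does not compare 8 with 14 days after dose 2.

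On exclusions, the adult OCV-S lots have 308 + 311 + 312 = 931 in Table S3 (PPS) against 327 + 322 + 323 = 972 in Table S2 (FAS). The difference is 41, or 4.2%, for all reasons together. That limits how many adults in these lots the rule can have removed, but says nothing about early samples that were kept.

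**Conclusion.** The point holds as an inconsistency between the endpoint definition and the sampling schedule. The permitted interval of 8 to 17 days and the unequal treatment of 15- to 17-day samples follow exactly from the printed windows. Calling those later samples acceptable rests on carrying the protocol's ±3 days over to dose 2, though the protocol itself accepts the same intervals after a Day 14 dose. The number of participants affected and the effect on the estimates cannot be derived from the protocol. The consequence is a blurred endpoint time point and inconsistent PPS membership. No bias between arms is shown, and nothing here suggests that the conclusions would be overturned. It should be corrected because the correction is cheap and the affected sample carries the primary and all secondary immunogenicity endpoints.

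**What to change.** In Table 2 (window and footnote), the Visit 4 heading in section 7.1.3 and the deviation list in section 7.2.15, state the Visit 4 blood-draw window relative to the actual second dose, for example 14 ± 3 days, which keeps the protocol's own tolerance. Use the same window (11 to 17 days since dose 2) for PPS membership, and have the data capture system compute the target dates. For a Day 14 dose the window stays at Day 25 to 31. Keep Day 28 for participants who receive no second dose.

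The Day 28 diary handover needs aligning. DC4 covers up to Day 27 and DC5 starts on Day 28, while Visit 4 could now fall as late as Day 34 instead of Day 31.

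If sampling is complete, apply the window to the recorded dates before database lock. If lock has passed, which the appended result tables suggest, report it as a sensitivity analysis together with the observed distribution of days from dose 2 to sample in each group. That would also settle how many participants are affected.

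The cost is wording in one table and two sections, a date calculation and a small diary-date adjustment, with no extra visits. The downside is that a few participants may move into or out of the PPS.

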**Table 5. Blood Sample Volume by Age**

| Age of participants | 1-5 Years          | 6-40 Years         |
|---------------------|--------------------|--------------------|
| Blood sample volume | Approximately 4 mL | Approximately 6 mL |

\*Minimum volume for 1-5 years old is 3 mL.

Each AE will be assessed according to the following method:

**Table 7. Assessment Method of Unsolicited Adverse Events**

| Assessment method                                     |                                          |
|-------------------------------------------------------|------------------------------------------|
| Unsolicited Adverse Events (Days 0-28 and Days 14-42) |                                          |
| Any other symptoms                                    | General observation/interview/diary card |

**Home visit/Phone call 3. Post 2nd dose 4-week Safety follow-up (Day 42 / Week 6  $\pm$  1 days)**

Each participant will be followed up for safety via home visit at Day 42. A visiting site staff will,

- 1) Verify and collect recorded DC5 and confirm with participant/parent(s)/LAR.
- 2) Record unsolicited AEs since last visit in eCRF. After Day 42, record concomitant medication history related to SAEs only.
- 3) Provide DC6 to document any adverse events (if any occurrence is there) during Day 42 to Day 181 before the next visit
- 4) Remind to bring DC6 at the next visit.
- 5) Remind to visit the site at Day 182.
- 6) Remind to contact investigator/ study staff if needed.

Home visit may be replaced by a phone call. Only a qualified healthcare professional (HCP) according to Nepal's definition of HCP (*i.e.*, registered physician, health assistant nurse practitioner, public health nurse, auxiliary health worker), should perform the call. A staff calling the participants will,

- 1) Check the participant's identification.
- 2) Call out all the unsolicited AEs listed in DC5 to participant(s)/parent/LAR so that the adverse events can be confirmed through the call.

- 3) Enter the unsolicited AEs and concomitant medications in DC5 into the eCRF when DC5 is collected.
- 4) Instruct participant(s)/parent/LAR to document any adverse events (if any occurrence is there) during Day 42 to Day 181 in DC6 and remind to bring DC5 and DC6 at Visit 5, Day 182.

Home visit/phone call maybe replaced by a site visit.

Each AE will be assessed according to the following method:

**Table 7. Assessment Method of Unsolicited Adverse Events**

| Assessment method                                     |                                          |
|--------------------------------------------------------------|------------------------------------------|
| Unsolicited Adverse Events (Days 0-28 and Days 14-42) |                                          |
| Any other symptoms                                           | General observation/interview/diary card |

#### **Visit 5. Post 2nd dose 24 week/6 months Safety follow up (Day 182 / Week 26 ± 5 days)**

Each participant will be followed up for safety.

- 1) Verify and collect recorded DC5 and DC6 and confirm with participant/parent(s)/LAR.
- 2) Record DC5 and DC6 in study database.
- 3) Only SAE and concomitant medication will be collected in the eCRF.
- 4) Instructed to contact investigator/study staff if needed.
- 5) Ensure source documents are completed before the participant/parent/LAR leave the study site.
- 6) For unresolved AEs, participants will be continued to be monitored after study ends.

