## 10.4 REPORTING PROCEDURES

### 10.4.1 ADVERSE EVENT RECORDING AND REPORTING

Adverse events, solicited AEs, and SAEs will be assessed at various study visits, documented in the source record, and recorded in the eCRF using accepted medical terms and/or the diagnosis that accurately characterize the event. When the diagnosis is known the AE term recorded in the eCRF will be the diagnosis rather than constellation of symptoms. The site PI or delegated SI will assess all AEs for seriousness, relationship to investigational product, severity, and other possible causes.

The timeframe for the collection of adverse events (AEs) occurring from the first administration of investigational product through to the end of the trial and will be collected as well as recorded in the source document and eCRF according to the MOP.

All AEs will be followed until they have resolved or are considered stable during the study. When an AE has not resolved by the current visit it will be documented in the eCRF as ongoing. If the event has a resolution date, this date must be recorded on the Adverse Event form, regardless of whether it falls within the AE reporting period.

Documentation will include date of onset, detailed description of the event and relevant history and physical examination, severity, attribution of the AE, treatment given and date the AE improved or resolved. The medical monitor will review the AEs reported regularly and clarify with PI or SI if there are queries. The data manager will review all AEs for consistency and provide summary of AEs to the medical monitor periodically. Non-clinically significant AEs still ongoing as the end of the study will be listed as continuing. SAEs continuing at the end of the study will be followed to resolution or stabilization. Details of AE reporting are included in the MOP.

The PI, sub-investigators, and site staff will exercise due diligence in ascertaining, accurately recording and promptly entering data on the eCRF for all AEs of all study participants. As data becomes available from the participant, the clinic adverse events should be recorded and entered by the site staff on regular basis. Site investigators will review, in a timely manner, the AE source data and determine the severity of the event and relation to the study agent. Site investigators will contact the study medical monitor for consultation of AEs as required.

---

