#### 13.1.2 PRIMARY SAFETY ENDPOINT

- Frequency of solicited adverse events within 7 days post vaccination, unsolicited adverse events within 28 days post vaccination, and SAEs after each dose during the entire study period in all ages and in each age stratum.

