#### 13.6.4 PRIMARY SAFETY ENDPOINTS ANALYSIS

The primary safety endpoint analyses are safety analyses of treatment emergent adverse events (TEAEs). TEAEs are defined for this trial as any AEs/ SAEs that occur on or after Day 0 following OCV-S or Shanchol™ administration. All TEAEs will be summarized by frequency, percentage and associated 95% confidence interval. The frequencies will also be presented separately by dose and will be depicted by system order class and preferred term. Additional frequencies will be presented with respect to maximum severity and relationship to investigational product. All serious TEAEs will also be summarized as above. Serious TEAEs will be presented in listings.

---

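### For participants phoned rather than visited at Day 42, the protocol contradicts itself on whether non-serious adverse events from Days 28–41 enter the eCRF

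*Protocol*

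**What the plan says.** Section 13.1.2 includes "unsolicited adverse events within 28 days post vaccination" in the primary safety endpoint. After dose 2 (Day 14), the second half of that window is captured on DC5. Visit 4 in section 7.1.3 reads: "Provide DC5 to document unsolicited adverse events (if any occurrence is there) from Day 28 to Day 41".

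The Day 42 contact is a home visit by default. DC5 is then collected and unsolicited events since the last visit are recorded in the eCRF. A phone call or a site visit may replace it. On the phone route the caller goes through the events on DC5 with the participant, who is told to bring DC5 and DC6 to Visit 5 on Day 182. The entry rule for this route is: "Enter the unsolicited AEs and concomitant medications in DC5 into the eCRF when DC5 is collected".

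At Visit 5, step 1 collects DC5 and DC6 and step 2 has both recorded in the study database. Step 3 then says: "Only SAE and concomitant medication will be collected in the eCRF".

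Table 2 marks unsolicited events at the Day 42 home visit/phone call and leaves the Visit 5 cell empty. It shows DC5 as collected at Day 42. Its footnote on the phone route stops at DC4: "For safety follow ups through phone calls, DC1,2 and DC 3,4 will be collected on V3 and V4, respectively". Section 10.4.1 takes the widest line, with adverse events "occurring from the first administration of investigational product through to the end of the trial" going into the source document and the eCRF.

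**The concern.** On the phone route DC5 reaches the site at the one visit whose eCRF rule excludes non-serious events. Two instructions say the card is to be entered. A third, placed directly after one of them, says that only serious events and medication are. Nothing in the text ranks them, and the footnote that should explain where phone-route cards go leaves DC5 out.

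Two sites could each follow the protocol and handle the same event differently. A site that reads step 3 literally would leave out events inside the primary safety window for participants who were phoned, while the same events would be recorded for participants visited at home. A site that follows the phone-call entry rule would include them, but only once the card comes back. What is at stake is complete and timely capture of one component of the primary safety endpoint.

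**Working it through.** **1. The window.** Dose 2 is on Day 14, and 14 + 28 = Day 42. This matches Table 7, which gives Days 14–42 for dose 2.

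**2. How the window is spread over the diary cards (section 7.1.3).**

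| Card | Days | Number of days | Returned on the phone route |
|---|---|---|---|
| DC3 | 14–20 | 7 | Day 28 (Visit 4) |
| DC4 | 21–27 | 7 | Day 28 (Visit 4) |
| DC5 | 28–41 | 14 | Day 182 (Visit 5) |

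The total is 7 + 7 + 14 = 28 days. The DC5 share is 14/28 = 50%. If Day 42 is counted as well, as Table 7 can be read, it is 14/29 = 48.3%. Day 42 itself then falls on DC6, so a corrected rule should refer to the window and not to the card number.

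**3. Time until the card is back on the phone route.**
- From the call: 182 − 42 = 140 days.
- With the visit windows (±1 day at Day 42, ±5 days at Day 182): shortest 177 − 43 = 134 days, longest 187 − 41 = 146 days.
- From the earliest event that DC5 can hold: 182 − 28 = 154 days.

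**4. The instructions side by side, for a non-serious event on Days 28–41 in a participant phoned at Day 42.**

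| Place | Does the event enter the eCRF? |
|---|---|
| Phone call 3, step 3 | Yes, when DC5 is collected |
| Visit 5, step 2 | Yes, if the study database is the eCRF; section 15.1 makes the eCRF the means of recording each participant's data |
| Visit 5, step 3 | No; no exception for DC5 |
| Table 2, unsolicited events row | Collected at Day 42, not at Visit 5 |
| Table 2, phone footnote | Silent on DC5 |
| Sections 10.3 and 10.4.1 | Yes, all adverse events |

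These cannot all be followed as written.

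**5. What is not exposed.** Serious events are reported throughout the study. Solicited events after dose 2 are on DC3 (Days 14–20), which is back by Day 28 at the latest. Only non-serious unsolicited events of phoned participants remain.

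**6. What cannot be computed.** The protocol does not say how many participants are phoned at Day 42, so the number of events at risk does not follow from it. The appended safety table gives unsolicited events after dose 2 in 88 of 2,529 participants (3.48%, 112 events), against 69 (2.73%, 101 events) after dose 1. It does not separate phone from home follow-up, so it neither shows nor excludes loss.

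**The case against.** The strongest reply is that step 3 of Visit 5 is a general line and that the more specific instructions prevail. Phone call 3 orders the DC5 events into the eCRF and Visit 5 step 2 orders the card to be recorded. On that reading step 3 concerns only the period after Day 42, just as Table 2 limits medication records to those related to serious events after Day 42. This is probably what was intended, but the text does not state the limit for adverse events, so the contradiction stands.

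The reply is right on several further points. Table 2 schedules unsolicited events at the Day 42 contact in either mode, Table 7 lists interview as a method, and the call is meant to confirm events. Section 10.4.1 asks for regular entry as data become available. Diary cards are source documents against which the eCRF is verified (section 14), so an omitted event could be recovered before database lock. On the other hand, the caller is told to read out what is listed on a card that the participant holds, and no step orders entry on the day of the call.

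Three stronger readings are tempting, and the documents do not support them:

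- **That half of the post-dose-2 unsolicited data is lost.** The text conflicts with itself; it does not uniformly bar entry. Home visit is the default, and the share phoned is unknown.
- **That the arms are compared with bias.** Nothing links contact mode to vaccine group. Allocation is randomised, assessors are blinded, and the safety comparison is descriptive (section 13.3).
- **That the rate of any treatment-emergent event is inflated by events up to Day 182.** The definition, "TEAEs are defined for this trial as any AEs/ SAEs that occur on or after Day 0", names no end day, but section 13.1.2 fixes the windows and the tabulation rule can sit in the SAP. In the appended table, all treatment-emergent events after dose 2 number 183, equal to 71 solicited plus 112 unsolicited.

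**Conclusion.** The point holds as an internal contradiction that needs to be reconciled. It concerns non-serious unsolicited events with onset on Days 28–41, which is half of the post-dose-2 diary window (14 of 28 days), in participants phoned at Day 42. A site following Visit 5 step 3 literally may omit events that belong to the primary safety endpoint. A site waiting for DC5 may enter them about 140 days after the call (134 to 146 with the visit windows).

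Late entry alone need not distort the final analysis, which takes place after all Day 182 visits. It can delay what reaches the safety committee's regular blinded review, whose timing is set in a charter that is not shown. The conclusion assumes that some participants are phoned at Day 42, which the protocol allows without saying how many.

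**What to change.** 1. **Visit 5, step 3.** State that the limit to serious events applies to events with onset after the 28-day window following dose 2, and that events inside the window, including those on DC5, are entered in full.
2. **Phone call 3.** Have the caller ask for all adverse events since Visit 4 and record them in the eCRF at the call, with DC5 used at Visit 5 for verification.
3. **Table 2 footnote.** Extend the phone-route sentence to DC5, so that it shows collection at Visit 5.
4. **Section 10.4.1.** Reconcile its recording period with the 28-day unsolicited window in section 13.1.2.

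The cost is a few changes of wording and a slightly longer call that is already planned. No visit, sample or analysis is added.
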